#### Quantitative real time PCR

Total mRNA will be extracted from PBMCs using TRIzol^®^ reagent (Thermofisher) following manufacturer's instructions. Using the one-step High Capacity RNA-to-cDNA Master Mix (Thermofisher, Carlsbad, CA, USA), 1 μg mRNA will be reversely transcribed following manufacturer's instructions in a total volume of 20 μl. About 2 μl of cDNA will be amplified using the TaqMan^®^ Gene Expression Master Mix and TaqMan^®^ Gene Expression Assay for frataxin (Applied biosystems, catalog no. Hs00175940_m1) in a StepOne real-time PCR. We will test 10 reference genes in order to choose the most stable in our experimental conditions using normfinder software. Relative expression will be calculated with the efficiency-calibrated model. The entire procedure will follow the Minimum Information for Publication of Quantitative Real-Time PCR Experiments (MIQE) guidelines.

#### Frataxin measurement

Peripheral Blood Mononuclear Cells will be extracted from 15 ml of EDTA anticoagulated whole blood and stored until analysis. PBMCs will be lysed with an extraction buffer (Abcam n.AB193970-50, Cambridge, UK), and total protein will be measured using the bicinchoninic acid assay. Each sample will be assayed in duplicate using a commercially available ELISA kit (Frataxin profiling ELISA kit, n.AB110173, Abcam, Cambridge, UK), and will be normalized with a standard curve using full length human frataxin (n.AB110353, Abcam, Cambridge, UK). This method will be used to measure frataxin at baseline and at weeks 4, 12, and 24 of the study.

### Electronic case report form

All variables will be stored in the electronic case report form (eCRF) of the study that will be specifically designed for the present study using Filemaker 19.5 software. It will be accessible through the web with a common browser. It will be hosted on a server based at the coordinating center with RAID type data protection. The eCRF will follow all indications of the Italian drug agency (AIFA) for non-profit clinical trials, including audit-log trail, data protection and backup, sheet freezing, and data unlock for deviations.

### Sample size calculation

Sample size calculation was performed based on our preliminary results of DMF treatment in patients with Multiple Sclerosis and is based on the estimated increase in FXN expression with the following assumptions derived from our preliminary data (Jasoliya et al., 2019). We previously found a significant +85% increase in the group treated with DMF compared to no increase in the control group (time^*^treatment interaction *p* = 0.02), which resulted in a partial eta square of 0.198. The sample size in this study was 14 patients treated with DMF and 13 with reference control treatment. The partial eta square of 0.198 results in an effect size of 0.497. Estimating the effect size based on preliminary data on MS patients is an underestimation of the potential effect of DMF in FRDA patients. Indeed, DMF can overexpress FXN through two mechanisms. One is the stimulation of nrf2 and the increase in transcription of several genes, including antioxidant genes and frataxin. This mechanism is clearly involved in MS patients treated with DMF. The second mechanism is the ability of DMF to induce transcription initiation and reduce transcriptional pausing in mutant *FXN* gene. This mechanism is unique to FRDA patients as it requires a mutated gene to be effective. In support of this, experiments in patients' lymphoblasts treated with DMF have found up to a +260% increase relative to baseline (Lynch et al., 2010), compared to our finding of +85% increase in MS patients treated with DMF. Based on this data, we calculated the appropriate sample size for this study using G^*^Power version 3.1.9.6. We used an ANOVA for repeated measures, within-between interaction, as the appropriate test. Effect size was set at 0.497, alpha error at 0.05, power at 0.8, number of groups 2, number of measurements 2, and non-sphericity correction 1. This results in a total population of 36 patients (18 treated + 18 placebo). We will prudently include 40 patients in total, allowing us to compensate for a lost at follow-up of up to 10% of randomized patients.

### Statistical analysis

All data will be preliminary tested for normality using the Kolmogorov–Smirnov test. Since quantitative real time PCR (qPCR) data are frequently not normal, a normalization attempt, using ln or log transformation, will be performed. qPCR data will be calculated as relative increases imputing a baseline expression level of 1.0. Main statistical analysis of both FXN expression and frataxin protein level will be conducted with a Generalized Linear Model (GLM) for repeated measures. GLM incorporates a two-way ANOVA for repeated measures and can accommodate a multivariate analysis of factors and covariates. Treatment with DMF or placebo will be considered as a factor, and baseline levels of frataxin will be considered as a covariate. FXN baseline expression will not be used in the model as it is already integrated using relative expression with common baseline. All other available data (sex, age, disease duration, GAA1, and treatment specific findings, etc.) will be preliminarily tested one by one as covariates. In case of resulting *p*-values < 0.1, they will be integrated in the final multivariate model with treatment as a factor. In case of a significant Maulchy's sphericity test, we will use the Greenhouse-Geisser correction. We will use a similar analysis approach for remaining secondary endpoints. This will include different time-points from FXN and frataxin, and other qPCR analysis, SARA, 9HPT, PRT, ADL/IADL, and EQ-5DVAS. The main analysis will be conducted with results from the core phase of the trial (20 patients treated with DMF and 20 with placebo) and will be used to draw conclusions on the efficacy of DMF. A secondary analysis will be conducted adding to the model patients from the extension phase that switched from placebo to DMF (total of 40 DMF vs. 20 placebo). This analysis will be considered as descriptive and not used to drive efficacy conclusions. For adverse events (AEs), we will perform a descriptive analysis of AEs including their distribution in DMF and placebo treated patients, AEs duration, severity, and connection to the study drug. To test if treatment with DMF increases the likelihood of having an AE, we will use a Generalized Linear Model with Poisson distribution and treatment as a factor. To test if a single AE is more frequently linked to DMF treatment, we will use the exact test of Goodness of fit, assuming an equal proportion of adverse events in the treatment and placebo group. This will be possible only for adverse events occurring at least once in both groups. For baseline variables a descriptive analysis will be performed, and difference between DMF and placebo patients will be tested with an unpaired *t*-test and chi-square test, depending on the variable. In case of non-normal distribution, a Mann–Whitney test will be used in place of a *t*-test. A two-sided significance level of 5% will be required to reject the null hypothesis that the outcome measures are the same before and after treatment, and for all other comparisons. The Bonferroni correction for multiple analyses will be used. Considering the primary endpoint and the phase of the trial, the analysis will be per protocol. Data will be analyzed using the SPSS 23 for MAC (IBM, Chicago, USA).

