Drug administration/accountability		X	X	X	X	X	X	X	X	X	X
Adverse events		X	X	X	X	X	X	X	X	X	X
Routine biochemistry	X	X	X	X	X	X	X	X	X	X	X
Hematology	X	X	X	X	X	X	X	X	X	X	X
Urine examination	X	X	X	X	X	X	X	X	X	X	X
Blood sampling for protein/RNA	X	X	X	X	X	X	X	X	X	X	X
Pregnancy test	X			X	X	X		X	X	X	X

ECG, electrocardiogram; SARA, Scale for the Rating and Assessment of Ataxia; m-FARS, modified Friedreich Ataxia Rating Scale; 9HPT, 9 hole pegboard test; ADL/IADL, activities of daily living/instrumental activities of daily living; EQ-5D, European quality of life scale; CPET, cardiopulmonary exercise test; EcoCG, echocardiography.

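### The repeated-measures GLM analyses only patients complete at every modelled visit; if all five core-phase RNA draws enter, more than about 2.1% missing draws would use up the 10% allowance

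*Protocol article*

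**What the plan says.** In the protocol article, Statistical analysis, the main analysis of both FXN expression and frataxin protein is to be "conducted with a Generalized Linear Model (GLM) for repeated measures". The section describes this as incorporating a two-way repeated-measures ANOVA, names SPSS 23 as the software, and adds: "In case of a significant Maulchy's sphericity test, we will use the Greenhouse-Geisser correction". The main analysis uses core-phase data from 20 patients per arm, and the section does not list the visits that enter. A similar approach is then applied to the remaining secondary endpoints, which include the other FXN and frataxin time points.

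The Primary endpoints section defines the outcome as the change in FXN expression at week 12 relative to baseline. The Sample size calculation says "We used an ANOVA for repeated measures, within-between interaction, as the appropriate test", with "alpha error at 0.05, power at 0.8, number of groups 2, number of measurements 2, and non-sphericity correction 1". It arrives at 36 patients and randomises 40, "allowing us to compensate for a lost at follow-up of up to 10% of randomized patients".

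In Table 2 (Visit schedule), the row "Blood sampling for protein/RNA" is marked at screening, baseline and weeks 1, 4, 8 and 12 of the core phase. The Frataxin measurement section limits the protein assay to baseline and weeks 4, 12 and 24.

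**The concern.** A repeated-measures ANOVA of this kind works on one row per patient and leaves out anyone with a gap in that row. If the model contains every core-phase visit, one failed RNA extraction at week 1 removes a patient whose baseline and week-12 values, which define the primary endpoint, are both valid.

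The sample-size allowance is stated for patients lost to follow-up and has no separate room for single missed samples. At stake are power for the primary comparison and an analysed set that depends on gaps at visits the primary endpoint does not use. Analysing all randomised patients instead of the per-protocol set would not cure this, because the deletion comes from the model.

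**Working it through.** **Inputs.** Effect size: "The partial eta square of 0.198 results in an effect size of 0.497" (Sample size calculation). Two-sided 5%: "A two-sided significance level of 5% will be required to reject the null hypothesis" (Statistical analysis). Required N 36, randomised N 40, two groups, two measurements (Sample size calculation). Core-phase RNA draws: baseline and weeks 1, 4, 8 and 12, so five (Table 2). The missing rate per draw, p, is **not in the documents**; it is an assumption, shown as a range.

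**Step 1: reproduce the plan's figures.** f = √(0.198/0.802) = 0.497. For the within-between interaction with two groups and two measurements, use a non-central F with 1 and N − 2 degrees of freedom and λ = f²(N − 2) = 0.247(N − 2). N = 36 gives power 0.804 and N = 40 gives 0.847. 36/0.90 = 40. The plan's figures reproduce.

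**Step 2: share of patients complete.** If k draws are required and each is missing independently with probability p, the complete share is (1 − p)^k. The 10% allowance is exceeded on average when p > 1 − 0.9^(1/k):

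- k = 5 (all core RNA draws): 2.1%, about 1 draw in 48
- k = 3 (frataxin: baseline, weeks 4 and 12): 3.5%
- k = 2 (baseline and week 12): 5.1%

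**Step 3: patients left of 40, with no other loss.**

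| p per draw | Five draws: patients left | Power | Two draws: patients left | Power |
|---|---|---|---|---|
| 1% | 38.0 | 0.83 | 39.2 | 0.84 |
| 2% | 36.2 | 0.81 | 38.4 | 0.83 |
| 3% | 34.3 | 0.78 | 37.6 | 0.82 |
| 5% | 31.0 | 0.73 | 36.1 | 0.81 |
| 10% | 23.6 | 0.60 | 32.4 | 0.76 |

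Example: 0.95⁵ = 0.774, and 40 × 0.774 = 31.0; 0.95² = 0.9025, and 40 × 0.9025 = 36.1. These are averages. With five draws, the chance that more than 4 of 40 patients are incomplete is 0.34 at p = 2% and 0.97 at p = 5%.

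**Step 4: if the 10% loss to follow-up also occurs**, 36 patients are left before sample gaps. Five draws then leave 36 × 0.904 = 32.5 at p = 2% (power 0.76) and 36 × 0.774 = 27.9 at p = 5% (0.68). Two draws at 5% leave 32.5 (0.76).

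**Step 5: the part due to the choice of model.** Baseline is needed to form relative expression, and a missing week-12 value gives no direct information on the week-12 contrast under any model. The avoidable loss therefore comes from weeks 1, 4 and 8 only. At 5% it is 36.1 − 31.0, about 5 patients.

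**Step 6: how many visits are intended?**

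- *For several:* a sphericity test has no content with two time points, and the main analysis refers to core-phase data without restricting them to week 12.
- *For two:* the endpoint compares baseline with week 12, the sizing uses two measurements, and other FXN time points are listed with the secondary endpoints.

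The text does not decide between them.

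**The case against.** The strongest reply is that the primary model has two time points, as the endpoint and the sizing suggest. The sphericity clause can be explained otherwise: the same paragraph covers frataxin, which has three core-phase assay times, and the secondary FXN analyses at further visits. On that reading a failed week-1 sample removes nobody from the primary analysis, and 5% missing per draw loses 9.8%, just inside the allowance. This stands as a possible reading. It does not remove the point, because the article never lists the modelled visits and the same complete-case approach is carried to the multi-visit secondary analyses.

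Other parts of the reply also stand. No missing rate is given. Independence is assumed, and gaps clustered in the same patients would cost fewer patients. The power figures apply a two-measurement formula to a five-visit deletion rule, so they show what the planned test would achieve with that many patients; they are not the power of a five-visit model. A screening draw also exists, although the article does not say it may replace a missing baseline.

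Handling of missing samples may be set out in a full protocol or analysis plan that is not shown, and its absence from the article is not the complaint. The complaint is that the article fixes a method that deletes partly observed patients.

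A reader might infer that ordinary gaps will exhaust the allowance, or that early gaps will differ by arm because of tolerability. The documents support neither: the first depends on an undocumented rate and on five visits being modelled, and the article gives no data on the second.

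**Conclusion.** The point holds conditionally. The specified procedure uses complete cases only, and the article leaves open whether the primary model has two time points or more. If all five draws are required, the 10% allowance fails on average above about 2.1% missing per draw. At an assumed 5% independent rate about 31 patients remain (power about 0.73), against about 36 (0.81) with two draws, so about 5 patients are lost to the choice of model. At 2% the allowance holds on average, provided that nobody is also lost to follow-up. For frataxin, with three core-phase assays, the threshold is 3.5%.

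It would go too far to say that the trial is underpowered or that the primary analysis will lose 23% of its patients. The change is still worth making: the method discards usable primary-endpoint data in any model with intermediate visits, and a better one is available in the same software.

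**What to change.** - State which visits enter the primary model and that the primary test is the treatment contrast at week 12. This also reconciles the two-measurement sizing with the sphericity wording.
- Replace the repeated-measures GLM with a linear mixed model for repeated measures (the MIXED procedure in SPSS) on log FXN expression at weeks 1, 4, 8 and 12, with treatment, visit, treatment by visit, GAA stratum and an unstructured within-patient covariance. A missed week-1, 4 or 8 sample then no longer removes a patient with baseline and week-12 values.
- If a baseline FXN covariate is wanted, use the un-normalised log baseline expression. Relative baseline is set to 1.0 for every patient and carries no information.
- For frataxin, use weeks 4 and 12 in the core phase, in line with the assay schedule. The secondary laboratory objectives also name week 1, and that should be reconciled.
- Measures with a single post-baseline core visit, such as SARA and 9HPT, do not need the multi-visit model.

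**Cost.** Wording, a little more analysis work, and no extra data or software. The drawback is that an unstructured covariance for four visits has 4 × 5/2 = 10 parameters to estimate from about 40 patients, so a simpler fallback structure should be named in advance in case the model does not converge.

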**Figure 2 F2:**
[figure not shown]
Study visit plan and procedures. V1, visit 1; V2, visit 2; V3, visit 3; V4, visit 4; V5, visit 5; V6, visit 6; V7, visit 7; V8, visit 8; V9, visit 9; V10, visit 10; ECG, electrocardiogram; Con Meds, concomitant medications; SARA, Scale for the Rating and Assessment of Ataxia; m-FARS, modified Friedreich Ataxia Rating Scale; FXN/mRNA, *FXN* gene mRNA measurement; PRT, PATA rate test; 9HPT, 9 hole pegboard test; ADL/IADL, activities of daily living/Instrumental activities of daily living; EQ-5D, European quality of life scale; CPET, cardiopulmonary exercise test; EcoCG, echocardiography.

The use of placebo is based on several factors. On one side, there is a need for a more accurate evaluation on the biochemical effect on FXN/mRNA and frataxin that can show fluctuations over time. For this reason, an increase of FXN/mRNA in an open-label trial could be erroneously attributed to treatment. The second reason is that secondary endpoints (CPET, Clinical scales, etc.) can show a clear placebo effect once patients take part in a clinical trial. There is no known risk of being in the placebo group as there is no treatment available for FRDA.

The study will begin with a screening visit where patients will sign their informed consent (Figure 2). We will then assess inclusion and exclusion criteria (Table 1). Patients fulfilling all inclusion and none of the exclusion criteria will undergo endpoint measurement and will enter the core phase of the study.

**Table 1 T1:** Inclusion and exclusion criteria.

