### Endpoints

#### Primary endpoints

The primary objective of the study is to evaluate the effect of DMF compared to placebo on *FXN* gene expression level considering the change from baseline to 12 weeks (core phase of the DMF-FA-201 study).

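### Baseline FXN is left out of the primary model on the ground that scaling to baseline already accounts for it; scaling is not adjustment, and adding log baseline FXN is a nearly free gain in precision

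*Protocol article*

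**What the plan says.** The primary endpoint (Primary endpoints) is the change in FXN expression from baseline to week 12, DMF against placebo. Under Statistical analysis, "qPCR data will be calculated as relative increases imputing a baseline expression level of 1.0". The main analysis is a repeated-measures GLM with treatment as a factor.

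On covariates, the same section says three things:

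- "baseline levels of frataxin will be considered as a covariate", meaning frataxin, which the section treats as a separate measurement from FXN expression.
- "FXN baseline expression will not be used in the model as it is already integrated using relative expression with common baseline".
- Other variables "will be preliminarily tested one by one as covariates" and are kept if p < 0.1. Baseline FXN is excluded by name, so this screen cannot bring it back.

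On scale, the section observes that qPCR data are often non-normal and says that "a normalization attempt, using ln or log transformation, will be performed".

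The data for the covariate exist. The Table 2 row "Blood sampling for protein/RNA" is marked at screening, at baseline and at every later visit. Under Trial design and intervention, the use of a placebo is justified partly because FXN mRNA and "frataxin that can show fluctuations over time".

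**The concern.** The plan treats division by baseline as if it were adjustment for baseline. Adjustment lets the data set the slope of week-12 FXN on baseline FXN. Division sets that slope to 1 on the log scale, whatever the data show. If week-12 values follow baseline less than one for one, as expected of a measure that fluctuates, patients who start high tend to show smaller relative increases and those who start low larger ones. That variation stays in the outcome as noise, and part of any chance baseline difference between two arms of 20 enters the treatment estimate.

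The stake is precision on the primary endpoint of a 40-patient, single-centre trial in a rare disease. The plan also adjusts for baseline frataxin while barring the baseline value of the outcome itself, which is the covariate most likely to help.

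A second, smaller matter concerns the untransformed scale. An individual ratio to baseline averages above 1 even when nothing has changed, so an arm's mean raw ratio is a poor description of drug effect.

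**Working it through.** **Inputs from the document (Sample size calculation).** Partial eta squared 0.198, f = 0.497, alpha 0.05, power 0.80, two groups, two measurements, N = 36, raised to 40 for 10% loss.

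**Assumed.** The correlation rho between baseline and week-12 log FXN, range 0.3 to 0.9. Equal variances at the two times unless stated. That f = 0.497 describes the scaled (change) analysis; the document does not say how the pilot outcome was scaled.

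**1. The plan's own figure.** f = √(0.198/0.802) = 0.497. With noncentrality f²(N−2) = 0.2470 × 34 = 8.40 on 1 and 34 df, power is 0.804 at N = 36. Then 36/0.9 = 40. Both figures reproduce. If all 40 are analysed, power is 0.847.

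**2. What the scaling leaves behind.** Let σ² be the variance of log FXN at each time.

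- Variance of log change: 2σ²(1−rho).
- Correlation of log change with baseline: −√((1−rho)/2), which is −0.59, −0.50, −0.39 and −0.22 at rho 0.3, 0.5, 0.7 and 0.9. It is zero only at rho = 1.
- If the arms differ by d in mean log baseline, the change-score estimate shifts by −(1−rho)d: 70%, 50%, 30% and 10% of d at those four values.

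If the common baseline means a group-level 1.0 rather than each patient's own, the time-by-treatment test with two time points is still a change-score test, so these results apply under either reading.

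**3. Gain from adding log baseline FXN.** The residual variance becomes σ²(1−rho²), so the variance ratio is (1−rho²)/[2(1−rho)] = (1+rho)/2. Power uses noncentrality f²(N−3)/[(1+rho)/2] on 1 and 33 df.

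| rho | Variance ratio | CI narrower by | Power at N = 36 | N for 80% power |
|---|---|---|---|---|
| 0.3 | 0.65 | 19% | 0.93 | 26 |
| 0.5 | 0.75 | 13% | 0.89 | 30 |
| 0.7 | 0.85 | 8% | 0.85 | 32 |
| 0.9 | 0.95 | 3% | 0.81 | 36 |

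Keeping the noncentrality at f² × 34 gives 0.94, 0.90, 0.86 and 0.82. Charging a second degree of freedom for the GAA stratum, with no benefit from it (f² × 32, 32 df), gives 0.92, 0.88, 0.84 and 0.80.

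**4. Unequal variances.** If the week-12 log SD is k times the baseline SD, the ratio is k²(1−rho²)/(1+k²−2·rho·k). The gain disappears when rho·k is near 1.

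- k = 1.2, rho = 0.7: 0.7344/0.76 = 0.97, power about 0.80.
- k = 1.4, rho = 0.7: 0.9996/1.00 = 1.00, no gain (power 0.79 to 0.80).
- k = 1.2, rho = 0.3: 1.3104/1.72 = 0.76, so a gain remains.

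**5. Does baseline frataxin make up the loss?** Simulation at 18 per arm (3,000 trials per setting, log-scale SD of change 0.6, both SDs equal) gave these powers:

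- Log ratio alone: about 0.81 to 0.83.
- Log ratio with a protein covariate correlated 0.3 or 0.6 with baseline FXN: 0.81 to 0.86.
- Log ratio with baseline FXN itself: about 0.94, 0.91, 0.86 and 0.83 at rho 0.3, 0.5, 0.7 and 0.9.
- Untransformed ratio, no covariate: about 0.75 to 0.77.

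**6. Raw-ratio inflation.** With no true change and a within-patient lognormal SD of s, the mean of week-12 over baseline is exp(s²): 1.04, 1.09, 1.17 and 1.28 at s = 0.2, 0.3, 0.4 and 0.5 (assumed values).

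**The case against.** The strongest reply is that nothing here breaks the trial. Allocation is randomised 1:1, the comparison is between arms, and a change or ratio outcome keeps that test valid. Power falls short only of what a better model would deliver; against its own target the plan is met. Neither rho nor the SDs are in the document, and there are credible values at which the gain is negligible. All of this stands, and it sets the weight of the point.

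Several stronger readings may tempt a reader, but the document does not support them:

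- **That the scaling biases the treatment comparison.** With no treatment effect, raw-ratio inflation is the same in both arms. It misleads only when one arm's mean ratio is read as drug effect. That caution is still worth giving, because the Statistical analysis section words its null hypothesis as equality before and after treatment.
- **That a baseline imbalance passes into the estimate in full.** Under equal variances only the fraction (1−rho) does.
- **That baseline FXN is thrown away.** It remains the denominator; what is lost is its use as a covariate.
- **That the log scale depends on the Kolmogorov–Smirnov result.** The text says a transformation will be performed and does not clearly make it conditional. It also does not commit the primary endpoint to one scale.
- **That two pre-dose FXN values are available and one is ignored.** Blood is drawn at screening, but nothing says that qPCR is run on that sample.

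The objection does not rescue the stated reason for the exclusion. Relative expression does not do the work of a covariate, and no other section restores baseline FXN to the model.

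**Conclusion.** The point holds as one about efficiency. The protocol's reason for excluding baseline FXN is statistically wrong, and the exclusion generally costs precision on the primary endpoint. With equal variances, the treatment-effect variance would fall by 35%, 25%, 15% and 5% at rho 0.3, 0.5, 0.7 and 0.9, taking power at N = 36 from 0.80 to about 0.93, 0.89, 0.85 and 0.81. There is little or no gain if rho is high, or if week-12 variance exceeds baseline variance enough to bring rho·k near 1. Baseline frataxin may recover part of the loss. These figures rest on an assumed rho and on the pilot effect size applying to the scaled outcome.

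Validity of the randomised test and the stated sample size are not in question. The point is therefore a free improvement: recommended, not a condition for the trial to proceed.

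**What to change.** Before unblinding, replace the sentence that excludes baseline FXN and specify the following for the primary endpoint:

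- Express FXN at every visit against a common calibrator sample, so that baseline keeps its own value and variance.
- Fix the log scale in advance.
- Regress week-12 log FXN on treatment, log baseline FXN and the GAA randomisation stratum (below 635; 635 or above).
- Report the back-transformed DMF-to-placebo ratio with its 95% CI.
- Do not interpret within-arm mean raw ratios as drug effect.

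Optionally, use the mean of the screening and baseline values as the covariate, if qPCR is run on both.

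The cost is a change of wording, a calibrator well on each plate, one degree of freedom for baseline FXN and one for the stratum. No visits or blood draws are added. If rho is very high and the stratum carries no information, those two degrees of freedom leave power about where it is now (0.80 at rho 0.9).

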## Methods and analysis

### Trial design and intervention

This will be a single-center trial with only one center activated at the AOU Federico II University Hospital. The study is composed of a screening visit and two sequential 12-week phases: a core phase and an extension phase (Figures 1, 2). During the core phase, patients will be randomly assigned to either a DMF or placebo group. During the extension phase, all patients will be treated with DMF.

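### The descriptive 40-versus-20 analysis puts the same 20 patients on both sides of the treatment factor and mixes two periods, so its interval and contrast are unreliable (minor)

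*Protocol article*

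**What the plan says.** All references are to the protocol article. In Statistical analysis, the main analysis uses "results from the core phase of the trial (20 patients treated with DMF and 20 with placebo"). The secondary analysis is then formed by "adding to the model patients from the extension phase that switched from placebo to DMF (total of 40 DMF vs. 20 placebo"). The next sentence limits its role: "This analysis will be considered as descriptive and not used to drive efficacy conclusions".

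The model into which the switchers are added is the one described earlier in the same section. For FXN expression and frataxin the analysis "will be conducted with a Generalized Linear Model (GLM) for repeated measures", and "Treatment with DMF or placebo will be considered as a factor, and baseline levels of frataxin will be considered as a covariate". For expression data, "qPCR data will be calculated as relative increases imputing a baseline expression level of 1.0". The section names no period term and no link between the two records of a switcher, and it does not say which baseline applies to extension data.

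Trial design and intervention states: "During the extension phase, all patients will be treated with DMF". So no patient is observed on placebo after week 12. The same section justifies the placebo arm partly by the behaviour of the outcome itself, referring to "FXN/mRNA and frataxin that can show fluctuations over time".

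**The concern.** Two things are wrong with a 40-versus-20 comparison built this way.

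- **The records are not 60 patients.** Each of the 20 patients randomised to placebo contributes once as placebo and once as DMF. A between-patient treatment factor takes the two records as coming from different people, so the variance of the difference is computed without their covariance.
- **The groups differ in calendar as well as treatment.** Half of the DMF records come from the extension and all placebo records from the core phase. Any change over time that is unrelated to DMF enters the treatment contrast. The protocol gives exactly this kind of fluctuation as a reason for needing placebo.

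At stake are the estimate, interval and any p-value of a secondary table, and the impression of sample size that a 40-versus-20 label gives. The trial's efficacy claim is not at stake.

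**Working it through.** **1. The count.** Core phase: 20 + 20 = 40 patients. Adding the switchers' extension records gives 20 + 20 = 40 DMF and 20 placebo, which is the plan's own figure: 60 records from 40 patients.

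**2. The contrast.** Let D be the mean change of the 20 patients on DMF in the core phase, P1 the mean change of the placebo patients in the core phase, and P2 the mean change of those same patients on DMF in the extension. With baseline set to 1.0, a two-time-point treatment-by-time test compares mean changes (leaving the frataxin covariate aside). The pooled contrast is

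D/2 + P2/2 - P1.

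**3. Standard error under independence.** In units of the SD of a change, assumed equal throughout:

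sqrt(1/40 + 1/20) = sqrt(0.075) = 0.274.

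**4. Correct standard error.** With rho the correlation between a patient's P1 and P2 changes:

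Var = (1/20)(1/4 + 1/4 + 1 - rho) = (1.5 - rho)/20.

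The protocol gives no rho, so the values are assumptions.

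| rho | Correct SE (SD) | 0.274 relative to correct |
|---|---|---|
| 0 | 0.274 | equal |
| 0.3 | 0.245 | 12% too large |
| 0.5 | 0.224 | 22% too large |
| 0.7 | 0.200 | 37% too large |
| -0.5 | 0.316 | 13% too small |

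**5. Why the sign of rho depends on the baseline.** If both changes are taken from the study baseline, they share that value with the same sign. With exchangeable errors, rho is about 0.5. If the extension change is taken from week 12, the week-12 value enters P1 with a plus and P2 with a minus, and rho is about -0.5. The protocol does not say which applies.

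**6. Error rates.** Two-sample t-tests on simulated data with no treatment effect and no period effect, 40,000 replicates, nominal 5%: about 1.7% rejections with a common study baseline and about 8.8% with re-baselining at week 12.

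**7. Period shift.** With a common study baseline, a shift d between the phases enters P2 only, so the contrast moves by d/2: 0.15 SD for d = 0.3 SD and 0.25 SD for d = 0.5 SD. With rho = 0.5 and d = 0.5 SD, simulated null rejection (20,000 replicates) is about 9.7%. With re-baselining at week 12, equal drift in the two phases cancels, and only a difference in drift remains.

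**8. The paired alternative.** The switchers' own contrast P2 - P1 has variance 2(1 - rho)/20. Its SE is sqrt(1.4/20) = 0.265 at rho 0.3, against 0.245 for the pooled contrast. At rho 0.5 both are 0.224. At rho 0.7 it is sqrt(0.6/20) = 0.173, against 0.200. Its bias from a shift d is the whole of d.

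**The case against.** The strongest reply is that the plan labels this analysis descriptive and rests efficacy on the 20-versus-20 core-phase comparison. That stands. A reader might infer that the trial's conclusion or its size is compromised, but the sample size calculation uses two groups and two measurements and does not draw on the pooled analysis.

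Second, the article never says that a switcher's two records are treated as independent. That also stands: it is an inference from the 40-versus-20 count and from treatment being a factor in a repeated-measures model, and a full analysis plan might handle the pairing. But the count is stated, the only model described is the one above, and following it as written leads to the problem.

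Four stronger readings are tempting and are not supported:

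- **That the intervals must be too wide.** This needs a positive rho. The direction is open until the extension baseline is fixed.
- **That the bias is about 7 points.** Halving the 13.7% rise in the earlier study's control group gives 6.85. That group were MS patients on fingolimod, an active drug, and the Sample size calculation section describes the control group as showing no increase. It does not measure drift in FRDA.
- **That a better within-patient comparison is being discarded.** Secondary endpoints already provides for comparisons in patients moving from placebo to DMF. Step 8 shows that the paired contrast is more precise than the pooled one only for rho above 0.5, and that it is fully confounded with time.
- **That the degrees of freedom matter much.** Using 58 rather than about 38 changes the critical t from about 2.02 to 2.00.

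What the descriptive label does not do is make the estimate and interval right. The section also applies its two-sided 5% level to all other comparisons, so a p-value may well be attached.

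**Conclusion.** The point holds as a minor flaw in a descriptive analysis. The double use of 20 patients and the lack of concurrent placebo in the extension follow directly from the protocol's statements.

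The size is conditional. Read as a between-group model with equal SDs, the stated standard error is 12% to 37% too large for rho from 0.3 to 0.7 and about 13% too small for rho of about -0.5. It is right only if rho is 0. With a common study baseline, the contrast absorbs half of any period shift. The protocol says that such fluctuation can occur but gives no figure for it. The core-phase analysis, the efficacy conclusion and the 40-patient sample size stand.

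**What to change.** Replace the 40-versus-20 comparison by one mixed model on the 40 patients over both phases:

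- patient as a random effect, or an unstructured within-patient covariance;
- current treatment as a time-varying term, visit or period, and the GAA stratum used in the randomisation;
- one study baseline for all records, stated explicitly.

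Include the extension records of patients who stay on DMF. Without them, once period is in the model, the switchers' extension data add nothing to the treatment estimate.

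Report N as 40 patients. State that no patient is observed on placebo after week 12, so period and treatment cannot be fully separated: the model does so only by assuming that the DMF effect does not change with time on drug. The switchers' change from week 12 to week 24 may be shown with its 95% interval, labelled as an uncontrolled summary.

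The cost is a few sentences in the analysis plan and a different model on data already being collected, with no extra patients, visits or assays.
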